## 4.6 Calendar of Events

| Parent Forms/Schedule             | Prior to Study Enrollment | Prior to discussion  | Discussion | After discussion  | 7 Day Follow-Up |
|-----------------------------------|---------------------------|----------------------------------|------------|-------------------------------|-----------------|
| Approached            | X                         |                                  |            |                               |                 |
| Informed Consent                  | X                         |                                  |            |                               |                 |
| Pre-Encounter Survey  |                           | X                                |            |                               |                 |
| Post-Encounter Survey             |                           |                                  |            | X                             |                 |
| Phone Survey                      |                           |                                  |            |                               | X               |
| EMR Review                        |                           |                                  |            |                               | X               |

1- Discussion is the encounter between the clinician and the parent where the child's risk and parents' options for screening are discussed.

2- When consent is provided by both the parent and clinician the encounters will be video and/ or audio recorded.

3- Parents enrolled will be captured in the remote data capture system. Parents found to be ineligible or who declined participation will be assigned a generic study ID by the study coordinator and the reason for ineligibility or that the parent(s) declined will be captured in a tracking log.

4- The pre-encounter survey may be administered after the discussion, if the flow of care for the enrolled parents' child does not allow for it to occur prior to the discussion of interest. These events will be captured in the remote data capture system.

| Clinicians Forms/schedule | Prior to Enrollment of Eligible Parents | Randomization | After discussion with each enrolled parent |
|---------------------------|-----------------------------------------|---------------|--------------------------------------------|
| Informed Consent          | X                                       |               |                                            |
| Clinician Survey          |                                         |               | X                                          |

## 4.7 Data collection

To assess the reach of the trial, study coordinators will record parents who are enrolled as well as those who were assessed for inclusion. The criteria for inclusion that the parents' child did not meet will be captured along with declines by the parent. This will allow us to measure participation and representativeness of the trial.

The enrolled parents' data will be collected via surveys prior to and after the encounter with the clinician where the disposition discussion took place. A study coordinator will collect data from the EMR for registration/randomization, and all subsequent data from time of initial visit for head trauma to 7 days after for follow-up to assess utilization and safety of the child of the enrolled parent(s). The types of resource utilization captured during the 7 day follow-up include: imaging data, outpatient visits and procedures, and inpatient hospitalizations (including admission and discharge dates, reason for admission, neurosurgical procedures, and discharge destination). The study coordinator will also obtain the PECARN risk estimate for each child whose parents provide consent. Parents will be provided a form on which to document this information at discharge from the ED or the hospital. This will allow for a more standardized collection of these data. We will also request that parents save all their healthcare bills that they receive during this 7-day period. The parent will be contacted 7 days after enrollment via phone (primary method of contact) for assessment of utilization and safety events. If the primary method of contact is not successful, the study coordinator will subsequently contact the parent(s) utilizing a secondary method

of contact that was obtained at time of consent (email, a secondary phone number, or mail) for completion of the 7-day assessment. Clinician's will be surveyed after each encounter with an enrolled parent.

Video/audio and audio recordings of the encounter will be collected, and the recordings will contain specifically the discussion of interest between the parents and the clinician regarding the results of the diagnostic investigations and management options along with the decision and actions that will be carried out. Criteria for an encounter to be recorded include consent from the parent, assent from the child, and consent from the clinician for recording. If the parent(s) or the clinician decline to be video recorded, we will request that an audio recording be obtained. Either the parent(s) or clinician can decline the audio recording or stop the recording at any time during the encounter. Regardless of whether video or audio recording are obtained, all other data on enrolled parents and their child and participating clinicians will be collected, and both the clinician and parent will be retained in the trial consistent with their consent to participate and intention to treat principles.

#### 4.7.1 Parents' collected characteristics

Preference: Parents will identify their preference in decision making style for their child prior to the encounter of interest with their treating clinician (Control preference scale). There are 5 levels of preference that parents choose from and that will be reported as a count and frequency for each item.

Health literacy: Parents will respond to 3 items that assess their health literacy prior to the encounter of interest with the treating clinician. The item 'How confident are you filling out medical forms by yourself?' will be classified into inadequate (response: not at all, little bit or somewhat) versus adequate health literacy (response: quite a bit or extremely). The other two items will be reported as frequencies of raw responses without categorization.

Subjective numeracy: Parents will respond to an 8-item questionnaire prior to the encounter of interest to assess their subjective numeracy (Subjective Numeracy Scale). All 8 questions will be summed (reversing the scale for the question on percentages and words) and averaged creating an overall score ranging from 1-6 where higher scores are indicative of higher levels of numeracy.

Demographics: Parents will self-report their ethnicity/race, annual income and highest education level obtained at time of enrollment.

#### 4.7.2 Parents reported outcomes

Decision: Parents' will report the decision made regarding their child's screening options.

Knowledge: In discussion with our parent representative and ED Patient Advisory Council, it became clear that a major focus of many parents of children with head injury will be whether their child experienced a concussion. It became apparent that the issue of whether the child has experienced a concussion is a lower priority to clinicians than whether the child has suffered a more serious structural brain injury, which is what can be detected by cranial CT. To meet the informational needs of parents, the decision aid defines and distinguishes a concussion as symptoms experienced by the child (such as headache, concentration, memory, judgment, balance and coordination) observed by others that can be diagnosed based on the history and physical examination alone, and a significant brain injury as structural damage to the brain resulting in blood collecting in spaces of the brain. Based on this design feature of the decision aid, we will assess parents' knowledge regarding the difference between a concussion and a traumatic brain injury. We will also assess parents' knowledge regarding their child's quantitative risk for a significant brain injury, the pros and cons of head CT compared to active observation, and what signs and symptoms parents should watch for in the next 24 hours that should prompt a return visit to the ED. Knowledge will be measured by means of a post-visit survey delivered immediately after the clinical encounter. Each knowledge question will provide the parent(s) with three options to respond (True, False, or Unsure), and the parent(s) will receive a score of 1 for a correct response and 0 for incorrect where any response of 'Unsure' will be considered incorrect. An overall score will be calculated by summing the correct responses and dividing by the number of questions asked. Surveys where parents' choose to not respond to any survey questions will be considered as missing. If at least one knowledge question is answered then the parent(s) will be considered as a responder and assessed for this outcome, where non-responses will be coded as incorrect.

Parent engagement in the decision making process: We will measure the degree to which clinicians engage parents' in decision making using the validated OPTION scale. The OPTION scale will be assessed by having 2 observers at the central coordinating site independently review and score 20% of the videos and upon agreement being found they will divide up the remaining videos of the encounters and review independently. The OPTION scale is composed of 12 items with a value of 0-4; they are summed, divided by 48 and then multiplied by 100. This creates a score that ranges from 0-100, where higher scores are reflective of a higher level of parental engagement.

Fidelity: We will measure the degree to which the intervention is implemented as intended in both intervention and control groups when reviewing the recordings. The recordings in the intervention group will serve as a measure of the fidelity with which the intervention was delivered as intended. We will use a checklist of elements present and absent for quantification of implementation.

Decisional conflict: We will measure the degree of conflict parents' experience related to feeling uninformed using the validated Decisional Conflict Scale (DCS). The 16 items of DCS are scored on a 0-4 scale; the items are summed, divided by 16 and then

multiplied by 25. The scale is from 0-100 where higher scores are reflective of parental uncertainty about the choice. There are 5 DCS subscales, where a DCS subscale consists of 3 questions (1 subscale of 4). If 2 of 3 (or 3 of the 4) questions within a subscale have responses then the parent would be considered as a responder and a score could be calculated. If more than one response per subscale is missing then that specific subscale is not calculated for the parents'. An overall DCS score can be calculated if no more than 5 responses are missing as long as each missing response falls into a different subscale.

Trust in the physician: We will measure parents' trust in their clinician using the validated Trust in Physician Scale (TPS). There are 9 items with a scale of 1-5, the items are subtracted by 1, summed, divided by 9 and then multiplied by 25. The scale ranges from 0-100 where higher values are reflective of higher levels of trust in their physician.

Satisfaction: We will assess parents' satisfaction by asking 5 questions regarding the acceptability and satisfaction regarding the way information was shared during the encounter using a 7-point Likert .

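### The only divisor given for the overall Decisional Conflict Scale score is 16, yet forms with up to five blank items may be scored; applied as written, each blank counts as no conflict

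*Protocol*

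**What the plan says.** All the scoring text is in Protocol section 4.7.2, under Decisional conflict.

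- **Formula.** "The 16 items of DCS are scored on a 0-4 scale; the items are summed, divided by 16 and then" multiplied by 25. No second formula is given.
- **Range and direction.** "The scale is from 0-100 where higher scores are reflective of parental uncertainty about the choice". Zero is therefore the favourable end.
- **Subscales.** There are five, four with three items and one with four. A subscale may be scored with one item missing, but no subscale formula or divisor is printed.
- **Incomplete forms.** "An overall DCS score can be calculated if no more than 5 responses are missing", provided that no two blanks fall in the same subscale. The sentence does not say what replaces a blank or what the total is divided by.

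Two other places bear on the point. For the knowledge score, section 4.7.2 does settle the value of a blank: "where non-responses will be coded as incorrect". Section 4.8.2 (Missing data) leaves a patient out of any outcome that is missing for that patient. It does not deal with items missing inside a scale that can still be scored.

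**The concern.** The formula fits a complete form. The completeness rule then admits forms with as few as 11 answered items. With no other divisor supplied, the plain way to follow the paragraph is to add the answered items and divide by 16. A blank then has the same effect as the answer 0, the lowest possible conflict.

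Three things follow. The score of a parent who skips items is too low. Such a parent cannot reach the top of the stated 0-100 range. And the comparison between arms comes to depend partly on how many items each arm leaves blank. Section 4.8.4 says that parents and clinicians cannot be blinded, so unequal item response is possible, although the protocol gives no evidence of it.

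Two programmers could also read the paragraph differently and give the same parent different scores on an outcome listed in the power table of section 4.8.3.

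**Working it through.** **Inputs.** From section 4.7.2: 16 items scored 0 to 4, divisor 16, multiplier 25, at most 5 blanks. From section 4.8.3: planned mean (SD) 36 (19) in usual care and 21 (21) with the decision aid, difference 15, power above 99%, 950 patients, about 75 clinicians, two-sided alpha 0.05. Assumed, because the protocol gives no figure: the share f of parents with blanks (2% to 20%) and the number k of blanks (1 to 5).

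**1. The plan's own figures.** Item count: 4 × 3 + 4 = 16. Maximum on a complete form: 16 × 4 / 16 × 25 = 100, as stated. Power: common SD = √((19² + 21²)/2) = 20.02; with 475 per arm the standard error is 20.02 × √(2/475) = 1.30, and 15/1.30 is about 11.5, so power exceeds 99.9%. It still does after 5% loss (902.5 patients) and with an assumed intraclass correlation as high as 0.20 (design effect about 3.3). The stated figure is reproduced.

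**2. One parent with k blanks.** Let the answered items average m.

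- Divisor 16: (16 − k) × m / 16 × 25.
- Divisor equal to the number answered: m × 25.
- Ratio: (16 − k)/16, so the proportional loss is k/16.

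| Blanks k | Loss k/16 | Score 36 becomes | Score 21 becomes | Maximum 100 becomes |
|---|---|---|---|---|
| 0 | 0% | 36.00 | 21.00 | 100.00 |
| 1 | 6.25% | 33.75 | 19.69 | 93.75 |
| 2 | 12.50% | 31.50 | 18.38 | 87.50 |
| 3 | 18.75% | 29.25 | 17.06 | 81.25 |
| 4 | 25.00% | 27.00 | 15.75 | 75.00 |
| 5 | 31.25% | 24.75 | 14.44 | 68.75 |

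**3. The comparison between arms.** If a share f of an arm leaves k items blank, its mean is multiplied by 1 − f × k/16. The smallest case is f = 0.02, k = 1 (factor 0.99875). The largest is f = 0.20, k = 5 (factor 0.9375).

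| Where the blanks occur | Formula | Smallest case | Largest case |
|---|---|---|---|
| Both arms equally | 15 × factor | 14.98 | 14.06 |
| Decision aid only | 36 − 21 × factor | 15.03 | 16.31 |
| Usual care only | 36 × factor − 21 | 14.95 | 12.75 |

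**4. Power in the worst case.** Take a difference of 12.75 and a design effect of 3.33, with the SD held at 20.02. The standard error is 1.30 × √3.33 = 2.37, and 12.75/2.37 is about 5.4. Power remains above 99%.

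**The case against.** The strongest reply is that the protocol nowhere says that a blank scores zero. The formula sentence describes the full 16-item instrument, and the sentence on incomplete forms is separate and names no divisor. Where the authors want a blank scored as zero, as for knowledge, they say so. Allowing at most one blank per subscale is also what one would write if answered items were to be averaged. On this view the gap is a scoring detail that a statistical analysis plan could fill.

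Much of this stands. A reader might infer that the plan orders division by 16 in every case, or fixes blanks at zero. The text does not go that far, and averaging may well be intended. For the subscales nothing is stated wrongly, since no divisor is given at all.

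What does not stand is that the matter is wholly left open. The protocol chose to fix the formula, the divisor, the range and the completeness rule here, and together they do not work: the only printed formula cannot give the stated range for the incomplete forms that the rule admits. A later plan that averaged answered items would have to depart from the only formula given. The knowledge rule just before it also makes a zero-for-blank reading easy to carry over. There a zero is the unfavourable value; on the DCS it is the favourable one.

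**Conclusion.** The point holds as a minor scoring fault. Applied as written, the formula lowers the overall score of a parent with k blanks by k/16, at most 31.25%. This is measured against the mean of that parent's answered items, so it assumes that the skipped items would have been answered much like the rest.

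Two stronger readings are not supported. The first is that non-response is turned into apparent benefit. Because the loss is proportional, equal missingness shrinks the difference, and so do blanks in usual care alone. Only an excess of blanks in the decision-aid arm can inflate it; the 16.31 in the table needs 20% of that arm to leave five items blank and nobody in usual care to leave any.

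The second is to set the 11.25-point fall (36 to 24.75) against the planned 15 points. That compares one parent at the limit of the completeness rule with a difference between arm means. The shift in an arm mean is much smaller: in the largest assumed case, 36 × 0.20 × 5/16 = 2.25 points.

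All the arm-level figures rest on assumed rates of blank items.

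**What to change.** Add one sentence to section 4.7.2: when the stated completeness rule is met, the overall DCS score is the sum of the answered items divided by the number of answered items, multiplied by 25. For a complete form this is identical to the present formula, and it restores the 0-100 range for incomplete ones.

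State the same form for the subscales as a clarification: divide by 2 when two of three items are answered, by 3 when three of four are, and multiply by 25.

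The cost is a sentence or two of protocol or analysis-plan wording and one line of scoring code. No new data are needed and the sample size does not change. The wording should be settled before DCS scores are compared by arm.

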## 1.0 Specific Aims

Our long-term goal is to promote evidence-based, patient-centered evaluation in the acute setting to more closely tailor testing to disease risk. As PCORI specifies, to “compare the use of risk stratification tools with usual clinical approaches to treatment selection or administration,” we propose the following Aim:

- Test if the decision aid, Head CT Choice, improves validated patient-centered outcome measures and safely decreases healthcare utilization.

Hypothesis: The intervention will significantly increase parents’ knowledge, engagement, and satisfaction, decrease the rate of head CT use, and decrease 7-day total healthcare utilization with no significant increase in adverse events.

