#### 4.8.3 Sample Size Estimation

Patient knowledge will be the primary outcome, as it was considered to be the most important endpoint by our patient representatives on the ED Patient Advisory Council. In order for the study findings to maximally impact practice and policy, however, we will need to be adequately powered to detect differences in the outcomes of interest to each of the stakeholders.

Accounting for a lost to follow-up rate of as high as 5% (there was 2% lost to follow-up in our pilot trial), approximately 75 clinicians (assuming an average of 15 clinicians/site) will enroll 950 patients. This will provide the following power to detect differences in each of the patient and stakeholder-important outcomes (using a 2-sided hypothesis test and an alpha of 0.05):

| Outcome (n = 950)                                                                                | Usual Care* | Decision Aid* | Difference | Power |
|--------------------------------------------------------------------------------------------------|-------------|---------------|------------|-------|
| Parent knowledge                                                                          | 44%         | 60%           | 16%        | >99%  |
| Parent engagement in the decision making process                                          | 7.0 (5.5)   | 27.0 (8.2)    | 20.0       | >99%  |
| Decisional conflict †                                                                     | 36 (19)     | 21 (21)       | 15         | >99%  |
| Trust in the physician                                                                    | 79 (20.0)   | 84 (20.0)     | 4.1        | 86%   |
| Parent satisfaction with the decision made (% agree or strongly agree they are satisfied) | 70.0 (26)   | 80 (26.0)     | 10.0       | >99%  |
| Safety (clinically-important traumatic brain injury) ‡                                    | 0.9%        | 0.9%          | 0%         | 82.5% |
| Proportion of children who undergo head CT §                                              | 49%         | 34%           | 15%        | 95%   |
| Healthcare utilization                                                                    | 8.3 (0.8)   | 6.8 (0.7)     | 1.5        | >99%  |

\*Estimates were determined from our completed randomized trial.

†Lower decision conflict scores indicate less conflict experienced by patients related to feeling uninformed.  

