#### 4.8.4 Allocation process

Clinicians will be randomized at the beginning of the study and, if necessary, when first treating an eligible patient. Clinician randomization will be stratified by study site and according to whether they are pediatric emergency clinicians or not. To maintain balance the randomization algorithm utilized will balance across the stratification factors dynamically as clinicians are enrolled.

Randomization will be assigned on a 1:1 basis across arms. Though we will not be able to blind parents and clinicians to use of the decision aid, we will blind the investigators and all nonclinical stakeholders to study arm.

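### Parent satisfaction is powered as satisfaction with the decision, but the only measure described asks about how information was shared, so the stated effect and power do not apply to it

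*Protocol*

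**What the plan says.** Three places in the protocol deal with parent satisfaction.

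- **1.0 Specific Aims** sets the hypothesis: "The intervention will significantly increase parents’ knowledge, engagement, and satisfaction". It does not say what the parents are to be satisfied with.
- **4.7.2 Parents reported outcomes** describes the measure: "asking 5 questions regarding the acceptability and satisfaction regarding the way information was shared during the encounter", "using a 7-point Likert" scale. It gives no item wording, no scoring rule and no cut-off.
- **4.8.3 Sample Size Estimation** has a power row labelled "Parent satisfaction with the decision made (% agree or strongly agree they are satisfied"). The entries are 70.0 (26) for usual care, 80 (26.0) for the decision aid, a difference of 10.0 and power above 99%. A footnote attributes the planning estimates to the earlier chest pain trial. Table 1 in section 3.2, which reports that trial, has no satisfaction row.

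**The concern.** The sections name different things to be rated. One is how the information was conveyed; the other is the choice between CT and observation. The decision aid is itself a way of conveying information, so the items in 4.7.2 come close to rating how the intervention was delivered, in a trial where parents cannot be blinded (4.8.4). A parent may like the presentation and be no happier with the choice, so an effect on one cannot be assumed for the other.

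Two things are at stake. The first is the planning figure: the 10-point difference and its power are stated for the decision, and the information-sharing items have no expected value, SD or power. The second is interpretation: the hypothesis does not say which construct a positive satisfaction result would refer to.

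**Working it through.** **Step 1. Compare the definitions.**

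| | 4.7.2 (measure) | 4.8.3 (power row) |
|---|---|---|
| What is rated | How information was conveyed | The decision |
| Instrument | Five 7-point items | Not stated |
| Summary | Not stated | Label: percentage agreeing. Entries: mean (SD) format |
| Expected effect | None | 70.0 (26) vs 80 (26.0) |

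Other parent outcomes in 4.7.2 do not fill the gap. The decision item records which option was chosen. The Decisional Conflict Scale concerns feeling uninformed and uncertainty about the choice. The trust scale concerns the physician.

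**Step 2. Inputs for the power check.**

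- From 4.8.3: "using a 2-sided hypothesis test and an alpha of 0.05"; "approximately 75 clinicians (assuming an average of 15 clinicians/site) will enroll 950 patients"; "Accounting for a lost to follow-up rate of as high as 5"%.
- From 4.8.4: "Randomization will be assigned on a 1:1 basis across arms".
- This gives 950/2 = 475 per arm. If the 5% loss comes off the 950, about 902 remain, or 451 per arm.
- Average cluster size: m = 950/75 = 12.67.
- The protocol gives no intracluster correlation (ICC). Values of 0.01 to 0.10 are assumed for illustration.

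**Step 3. Reproduce the stated figure as a comparison of means.**

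Power = Φ(δ/SE − 1.96), with SE = SD × √(2/n).

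- SE = 26 × √(2/475) = 1.687
- δ/SE = 10/1.687 = 5.93
- Power = Φ(3.97) = 99.996%. With 451 per arm it is 99.99%.

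The entry above 99% is reproduced.

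**Step 4. Recompute on the labelled scale, 70% versus 80%.**

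Power = Φ((d − 1.96 × SE0)/SE1), with d = 0.10 and pooled proportion 0.75.

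- SE0 = √(2 × 0.75 × 0.25/475) = 0.02810
- SE1 = √((0.70 × 0.30 + 0.80 × 0.20)/475) = 0.02791
- Power = Φ((0.10 − 0.05507)/0.02791) = Φ(1.61) = 94.6%. With 451 per arm it is 93.6%.

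The entry above 99% is not reproduced.

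**Step 5. Allow for clustering by clinician.**

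Design effect = 1 + (m − 1) × ICC; effective n per arm = 475/design effect.

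| Assumed ICC | Design effect | Effective n per arm | Power, means | Power, 70% vs 80% |
|---|---|---|---|---|
| 0 | 1.00 | 475 | >99.9% | 94.6% |
| 0.01 | 1.117 | 425 | >99.9% | 92.2% |
| 0.05 | 1.583 | 300 | 99.7% | 80.9% |
| 0.10 | 2.167 | 219 | 98.1% | 67.8% |

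**Step 6. Power for the items described in 4.7.2.** None can be computed, because the protocol gives no mean, SD or responder rate for them.

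**The case against.** The strongest reply is that 4.7.2 is a one-sentence summary of five questions whose wording is not given, and the post-encounter survey is not reproduced. One question may well ask about the decision. Knowledge is primary, so satisfaction is not the designated main endpoint, and item scoring is commonly left to an analysis plan. As a comparison of means the stated power holds: at the planned 10 points it is 99.7% even at an assumed ICC of 0.05.

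Much of this stands, and it rules out three stronger readings that a reader might infer.

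- **That decision satisfaction is never collected.** The documents support only that no described item collects it.
- **That power for decision satisfaction is poor because the true effect may be much smaller than planned.** No smaller effect appears in the protocol, and a smaller effect would lower power for any construct. That would not measure this inconsistency.
- **That false-positive error is inflated because any one of the five items could carry the claim.** The protocol states no such rule, and its silence on scoring is not by itself a fault here.

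The reply does not remove the contradiction. Both definitions are fixed in the protocol and differ on what is rated. An analysis plan could choose one, but the other passage would still be wrong.

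**Conclusion.** The concern holds as an inconsistency of definition. The effect size and power in 4.8.3 are stated for satisfaction with the decision, the only measure described is satisfaction with information sharing, and 1.0 does not say which is meant. The planning figures therefore cannot be carried over to the items described.

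The power row also mixes scales. Its value above 99% is that of a continuous score with SD 26. Read as the percentage in its label, power is about 95% at 950 without clustering and about 92% to 68% across ICCs of 0.01 to 0.10. That range depends on the assumed ICC, equal cluster sizes and a normal approximation.

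The reach is limited to one hypothesised, non-primary outcome. The definition of the primary knowledge outcome is unaffected. The point should be corrected, but it does not threaten the trial's main conclusion.

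**What to change.** Use one construct in 4.7.2 and 4.8.3, by either route:

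1. **Keep information sharing.** Rename the row in 4.8.3 to match, name in advance one summary of the five items as the quantity tested, and state its expected difference and power.
2. **Keep the decision.** Name the post-encounter item on satisfaction with the decision as the endpoint in 4.7.2, and treat the information-sharing items as descriptive.

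Under either route, state whether the endpoint is a mean score or a percentage, define the cut-off on the 7-point scale if it is a percentage, and give the power on that scale with the ICC assumed. Limit the satisfaction part of the hypothesis in 1.0 to the construct chosen.

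The cost is protocol wording, plus at most one survey item under the second route if none exists. The sample size need not change on this account, though the restated power may be less favourable.
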